## Abstract

Patients with chronic heart failure (CHF) and reduced left ventricle ejection fraction benefit from cardiac resynchronization therapy (CRT) and implantable cardioverter defibrillator (ICD). However, increasing numbers of patient with CRT and ICD devices produce overload of cardiology centers where patients are admitted to ambulatory visits. This study aims to find multivariate model predicting the requirement for ambulatory follow-up of cardiac implantable electronic devices (CIEDs).

The LUCY study is an observational, cohort, prospective, 2-stage trial. As equal number of patients (300) will be included in the first and the second part of the study, finally, 600 patients will be included in the study. The inclusion criteria will be: age between 18 and 90 years, CHF (New York Heart Association classes I–III) and implanted ICD or CRT at least 30 days before study inclusion. The exclusion criteria will be dementia and other conditions impeding cooperation during the study. All patients included in the study will undergo standard ambulatory visit. Primary endpoint will be defined as any ambulatory visit qualified as necessary due to patient's condition or device malfunction diagnose by the cardiologist: any change in pharmacotherapy related to patient's clinical status assessed during the visit, any change in tachyarrythmia counter or discriminator status, any change in tachyarrythmia threshold, presence of ventricular undersensing or oversensing, presence of atrial or ventricular ineffective pacing, or device's pocket infection. Secondary endpoint will be defined as any ambulatory visit qualified as necessary due to the alarm identified via Medtronic CareLink Express (MCLE): sustained or treated ventricular tachyarrythmia, any not previously diagnosed supraventricular tachyarrythmia, or elective replacement indicator.

Our study is the first attempt of implementation of the machine learning and elements artificial intelligence in health care optimization of patients with CIED. The LUCY will be an open product, available for additional testing and improvement with supplementary functionalities: quality of life assessment, teleconsultation, video-streaming, automated imagine recognizing.

## Introduction

1

Patients with chronic heart failure (CHF) and reduced left ventricle ejection fraction benefit from implantable cardioverter defibrillator (ICD).^[1]^ Among them, individuals with electrocardiographic signs of left ventricle contraction asynchrony are candidates for cardiac resynchronization therapy (CRT).^[2]^

Patients with cardiac implanted electronic devices (CIEDs), both ICD and CRT, require long-term observation. Most of them, especially in Europe, are regularly monitored during standard ambulatory visit at least twice a year.^[3]^ However, increasing numbers of patients with CRT and ICD devices lead to overload of referral cardiology centers. According to the latest publications most standard ambulatory visits are unnecessary: do not provide any additional information nor result in changes in pharmacologic treatment or significant reprogramming of the device.^[4]^ Moreover, high number of ambulatory visits reduces time and sources necessary to provide better therapy for the most complicated subjects.^[5,6]^

Currently used devices, besides cardiac pacing and delivering low- and high-energy antitachyarrythmia therapies, record patient's heart rate, activity, and many other parameters directly related to patients's hemodynamics. Whereas there are technologic possibilities for remote monitoring proven to be effective in identifying the device's damage and high risk of CHF exacerbation remote monitoring can be a solution for overload health care providers to optimize patients’ management and therapy.^[5–8]^ On the contrary, currently used remote monitoring services provide an “information noise” that is tremendous volume of data about device, involve medical staff's continuous attention, and limit clinical information.^[9]^ For this reason, an additional contact with patient for clinical information is essential to fully assess patient's health status.^[3,5,6]^ Therefore, we shall provide a new system of remote monitoring available to integrate data from implanted devices and health status reported by patient.

The aim of the study is to develop an interactive patient's assistant called LUCY and a multivariate model predicting the requirement of ambulatory follow-up of patients with ICD or CRT device.

## Methods

2

### Trial design

2.1

The LUCY study is an observational, cohort, prospective, 2-stage trial.

Designed in the study interactive patient's assistant, also called LUCY will be a mobile application, a database and a machine learning system operating as a data integrator. During the first stage of the study LUCY will be initiated. The relevant parameters for patient's endpoints prediction will be collected from data from remote device's interrogation via Medtronic CareLink Express (MCLE) system and health status reported by patients. Implemented real-time self-learning algorithm will predict the necessity of ambulatory visit. In the second stage of the study, the effectiveness of LUCY's prediction of patient's endpoints will be assessed.

### Ethics and registration

2.2

This protocol has been reviewed and approved by the Institutional Review Board of the Medical University of Warsaw, number AKBE/233/2017. The protocol identification number at ClinicaTrials.gov is NCT03474315. The study will be conducted following the principles of the Declaration of Helsinki. Data monitoring committee is not planned in the study as it is an observational study.

### Study population

2.3

As equal number of patients (300) will be included in the first and the second part of the study, finally, 600 patients will be included in the study.

Participants will be recruited among patients who are under the outpatient care of reference cardiology center and sign informed consent. The inclusion criteria are: age between 18 and 90 years, CHF (New York Heart Association classes I–III) and implanted Medtronic (Minneapolis, MN) ICD or CRT at least 30 days before study inclusion. The exclusion criteria are dementia and other conditions impeding cooperation during the study.

All patients will undergo remote control using MCLE system and record patient-reported clinical outcomes just before the ambulatory visit. Patients reported data will be collected just after remote device interrogation with a mobile device through the dedicated module of the LUCY.

All patients included in the study will undergo standard ambulatory visit in the referral outpatient clinic immediately after evaluation by LUCY. Every patient will be examined by an expert cardiologist blinded for result of LUCY's evaluation. Due to patient's physical examination and device interrogation cardiologist may indicate device reprogramming, changes in medications or patient's hospitalization. Cardiologist's decisions will be referral to results of LUCY's evaluation and will be considered as real-time data for machine-learning. Study protocol is presented in Figure 1.

**Figure 1 F1:**
[figure not shown]
Study protocol. CRT = cardiac resynchronization therapy, ICD = implantable cardioverter-defibrillator, MCLE = Medtronic CareLink Express, NYHA = New York Heart Association.

During the study, every LUCY's module will be optimized and maintained by an interdisciplinary team to perform data acquisition and real-time implementation of automated algorithm modification to predict unnecessary ambulatory visit.

### Study endpoints

2.4

Primary endpoint was defined as any ambulatory visit qualified as necessary due to patient's condition or device malfunction diagnose by the cardiologist: any change in pharmacotherapy (modification of agents or doses) related to patient's clinical status assessed during the visit, any change in tachyarrythmia counter or discriminator status, any change in tachyarrythmia threshold, presence of ventricular undersensing or oversensing, presence of atrial or ventricular ineffective pacing, or device's pocket infection.

Secondary endpoint was defined as any ambulatory visit qualified as necessary due to the alarm identified via MCLE: sustained or treated ventricular tachyarrythmia, any not previously diagnosed supraventricular tachyarrythmia, or elective replacement indicator.

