### Outcome assessment

2.5

The outcome of the study is a true positive result of the LUCY's estimation in predicting primary and secondary endpoint in the second stage of the trial.

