### Machine learning

2.6

Data collected from the first 300 patients will be analyzed with neural net created by interdisciplinary team of medical and technology departments. Machine learning will be performed using the R programming language (v. 3.4.3). Afterwards, the neural net will be updated real-time after every patient's assessment to predict primary and secondary endpoint with the highest effectiveness.

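### Hospitalisation is a reference decision in section 2.3 but belongs to neither endpoint in section 2.4, so an admission with no listed finding or alarm is labelled as an unnecessary visit

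*Protocol article*

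**What the plan says.** Section 2.3 (Study population) describes the visit that follows LUCY's evaluation. After examination and interrogation, the blinded "cardiologist may indicate device reprogramming, changes in medications or patient's hospitalization". The next sentence gives these decisions their role: "Cardiologist's decisions will be referral to results of LUCY's evaluation and will be considered as real-time data for machine-learning". The wording is loose, but its sense is that the decisions are the reference for LUCY's result and also feed the learning.

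Section 2.4 (Study endpoints) opens the primary endpoint as "any ambulatory visit qualified as necessary due to patient's condition or device malfunction diagnose by the cardiologist". A colon and a list follow. The list begins with "any change in pharmacotherapy (modification of agents or doses) related to patient's clinical status assessed during the visit", goes on to changes in tachyarrhythmia counter, discriminator or threshold settings, and ends with "presence of ventricular undersensing or oversensing, presence of atrial or ventricular ineffective pacing, or device's pocket infection". The secondary endpoint covers visits made necessary by an MCLE alarm: "sustained or treated ventricular tachyarrythmia, any not previously diagnosed supraventricular tachyarrythmia, or elective replacement indicator". The Abstract gives essentially the same two lists. Hospitalisation is in neither of them, and neither has an item for other reasons.

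Section 2.5 (Outcome assessment) scores the study on a "true positive result of the LUCY's estimation in predicting primary and secondary endpoint in the second stage of the trial". Section 2.6 (Machine learning) says that "the neural net will be updated real-time after every patient's assessment to predict primary and secondary endpoint with the highest effectiveness".

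**The concern.** LUCY's stated purpose is to identify visits that need not take place, so its reference label has to mark as necessary every visit at which the cardiologist did something that mattered. Section 2.3 treats admission as one of three possible outcomes of the visit. Section 2.4 gives it no place. If the endpoints are applied as written, a patient admitted from the visit for a reason outside the lists becomes a negative case, both for training and for scoring.

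Two things follow for such a visit. In training, the net is told that this pattern of device data and self-report belongs to an unnecessary visit. In stage 2, clearing the patient agrees with the label and the miss does not show in the result. A false all-clear on a patient who is then admitted is arguably the most important error such a tool can make, and for these visits the planned scoring cannot detect it.

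**Working it through.** No figure stated in the article depends on this point, so there is no figure to reproduce. The check compares the sections and then gives an illustration of size.

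**Step 1: decisions against endpoint components.**

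| Decision in section 2.3 | Primary endpoint, 2.4 | Secondary endpoint, 2.4 |
|---|---|---|
| Medication change | Listed | Not listed |
| Device reprogramming | Listed for tachyarrhythmia settings; sensing and pacing faults are listed as findings | Not listed |
| Hospitalisation | Not listed | Not listed |

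**Step 2: which admissions are still captured.** An admitted patient is labelled positive if the visit also shows a drug change related to clinical status, a listed tachyarrhythmia setting change, a sensing or pacing fault, pocket infection, or one of the three MCLE alarms. Only admissions with none of these are mislabelled.

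**Step 3: does the label reach the result?** Yes. Section 2.6 trains the net to predict the two endpoints and section 2.5 scores it on them. The mislabelled visits therefore enter both steps as negatives.

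**Step 4: illustrative size.** Inputs:

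- Visits in stage 2: n = 300 (section 2.3).
- Outcome prevalence: 30% (section 2.7.1), so 300 × 0.30 = 90 primary-endpoint visits.
- Share of visits ending in hospitalisation: h = 1% to 5%. This is an assumption; the documents give no rate.
- Share of those that meet no listed component: u = 10% to 100%. This is also an assumption.

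Mislabelled visits m = n × h × u. Their share of necessary visits, taking the primary endpoint plus these visits as the total, is m / (90 + m).

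| h | u | m | m / (90 + m) |
|---|---|---|---|
| 1% | 10% | 300 × 0.01 × 0.10 = 0.3 | 0.3 / 90.3 = 0.3% |
| 2% | 50% | 300 × 0.02 × 0.50 = 3 | 3 / 93 = 3.2% |
| 5% | 50% | 300 × 0.05 × 0.50 = 7.5 | 7.5 / 97.5 = 7.7% |
| 5% | 100% | 300 × 0.05 × 1.00 = 15 | 15 / 105 = 14.3% |

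Visits that are necessary only through an alarm would enlarge the denominator, so the shares in the last column would then be somewhat smaller.

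**The case against.** **The lead-in may already cover admission.** The primary endpoint speaks of necessity due to the patient's condition, which could be read to include hospitalisation. But a colon and a specific list follow and define the phrase. If admission was meant, the text does not secure it, and two assessors could code the same visit differently.

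**All cardiologist decisions feed the learning.** Section 2.3 does say this, so hospitalisation may enter as data. The targets in sections 2.5 and 2.6 are still the endpoints. If the decisions themselves were the labels, the article would contain two different reference standards, which would need reconciling as well.

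**The article is a condensed account.** That excuses missing detail. Here the endpoint is set out as a complete list, in both the Abstract and section 2.4, and the point is about what that list fixes.

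**The affected visits may be rare.** This stands. Many admissions will also involve a drug change, a device finding or an alarm, and the low end of the range is effectively zero.

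A reader might also infer more than the documents support:

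- *That correct calls on alarm-only visits become false positives.* These visits are the declared secondary endpoint, on which LUCY is also trained and scored. The inference needs a single output scored against the primary endpoint alone, and the article does not say that.
- *That LUCY learns to clear the sickest patients.* Only admissions outside every listed component are mislabelled, and nothing suggests that these make up most admissions.
- *That the partial coverage of reprogramming is an error of the same kind.* The Introduction describes unnecessary visits as those without significant reprogramming, so counting only some changes looks deliberate.
- *That participants are put at risk.* Every patient has the full visit with a blinded cardiologist.

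**Conclusion.** The concern holds for hospitalisation alone. Section 2.3 makes it a reference decision, section 2.4 leaves it out of both endpoints, and the training and scoring targets carry the omission into the result. The wrong labels are confined to admissions with no drug change, listed device item, pocket infection or alarm; the other labels are unaffected.

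The size cannot be derived from the documents. Under the assumed ranges it is about 0.3 to 15 of 300 stage-2 visits, and the same range applies to the 300 stage-1 visits if the same rates hold there. The text comparison is firm, whereas the count rests wholly on the two assumed shares. The omission should be fixed because of the kind of visit affected and because correction is cheap, but it does not undermine the design.

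**What to change.** Reconcile sections 2.3 and 2.4, and the Abstract with them:

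1. Add hospitalisation indicated by the cardiologist at the visit as a component of the primary endpoint.
2. State that a visit counts as unnecessary only if it meets neither the primary nor the secondary endpoint.
3. State that an admission prompted by an MCLE alarm counts in both endpoints.

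The cost is small if this is done before labels are assigned. The decision is already made at the visit, so no new procedure or data item is needed and patient care does not change. Made later, it would require relabelling and retraining. There are two downsides. Prevalence of the primary endpoint may rise slightly above the 30% assumed in section 2.7.1: by m / 300, which is 0.1 to 5 percentage points over the range above, plus any admissions captured so far only through an alarm. The two endpoints will also overlap for alarm-prompted admissions, which is why item 3 is needed.

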### Outcome assessment

2.5

The outcome of the study is a true positive result of the LUCY's estimation in predicting primary and secondary endpoint in the second stage of the trial.

#### Data collection tools

2.5.1

##### Medtronic CareLink Express

2.5.1.1

The effectiveness of MCLE system was previously assessed and results were published.^[4]^ All participants will be trained in using MLCE system. Device remote interrogation will be performed just before ambulatory visit via MCLE station located at the ambulatory clinic. Data collected via MCLE include: supraventricular- and ventricular-tachyarythmia episodes, ICD therapies, signal amplitudes, percentage of paced rhythm, patient's activity, thoracic impedance and fluid status, heart rate variability, mean heart rate at night and day, and battery status.

##### LUCY's module for patient self-reported clinical status

2.5.1.2

Important module of the LUCY platform will be a tool for patients’ health status self-evaluation. It was designed as an interactive tool compiling proprietary questionnaires exploring different domains quality of life, factors affecting health (especially CHF) status, medical adherence, and device pocket status.

The data will be inputted using a tablet and dedicated web page. It should be emphasized that the group of patients with CIED is diverse: people between the ages of 18 and 90 years, for various society groups, which additional comorbidities or disabilities. The web page is very user-friendly and adjusted for people with vision defects, allowing assessment expressed on a scoring scale.

The very first patients included into the study will be asked to fulfill questionnaires validated for the Polish population:the World Health Organization Quality of Life Test - BREF to assess the quality of life of people under 65 years of age and adequately the World Health Organization Quality of Life Test - AGE for older people,^[10]^the Minimum European Health Module, a set of 3 general questions characterizing 3 different concepts of health: self-perceived health, chronic morbidity, and activity limitations,^[11]^the Beck depression inventory for people under 65^[12]^ and the geriatric depression scale for older people,^[13]^the adherence in chronic diseases scale to assess the adherence to prescribed pharmacologic treatment,^[14]^authors’ questionnaire of CHF symptoms exacerbation, andqueries about device pocket's clinical status.

While the time needed to report patient's clinical status is a key issue, the neuronal net will be focused on limiting number of queries necessary to assess patient's clinical status. Limiting queries with every iteration requests implementation of an additional condition into machine-learning schema and interaction between user and built-in assessment center after every patient's answer.

### Machine learning

2.6

Data collected from the first 300 patients will be analyzed with neural net created by interdisciplinary team of medical and technology departments. Machine learning will be performed using the R programming language (v. 3.4.3). Afterwards, the neural net will be updated real-time after every patient's assessment to predict primary and secondary endpoint with the highest effectiveness.

### Statistical methods

2.7

#### Sample size calculation

2.7.1

During the survey planning, we calculated the sample size required to assess the correlation between input data and primary outcome as 311, due to results of previously performed and published study (alpha = 0.01, study power = 0.95, the odds ratio for outcome indication = 3.3, outcome prevalence = 30%).^[4]^ We used G∗Power software 3.0.1.0 downloaded from http://www.gpower.hhu.de [S1]. The final number of subjects planned to input into the study is a double of calculated size (one for each stage of the trial).

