#### Statistical analysis

2.7.2

All the data will be analyzed in R (v. 3.4.3). Continuous variables will be presented as means and standard deviation while categorical variables as number and percent of subjects. For categorical variables, differences between patients will be analyzed using Pearson Chi-squared test. For continuous variables, the Kolmogorov–Smirnov test will be applied to check the distribution of data. In the case of normally distributed data independent *t* test will be used to compare patients, whereas Mann–Whitney *U* test will be used for non-normal distributions. Effectiveness of analyzed parameters and composite parameters in indicating the patient's fulfilling primary and secondary outcomes will be assessed using logistic regression. For all analysis, *P*-value <.05 will be considered significant.

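### Section 2.7.1 says enrolment is twice the calculated 311 (622), but the article plans 300 per stage (600); each stage is 11 below its own calculated size, with a small loss of power

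*Protocol article*

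**What the plan says.** The protocol article fixes the sample size in three places.

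- Section 2.7.1 (Sample size calculation): "we calculated the sample size required to assess the correlation between input data and primary outcome as 311". The inputs are "alpha = 0.01, study power = 0.95, the odds ratio for outcome indication = 3.3, outcome prevalence = 30" per cent. The calculated size is then tied to enrolment: "The final number of subjects planned to input into the study is a double of calculated size (one for each stage of the trial".
- Section 2.3 (Study population): "As equal number of patients (300) will be included in the first and the second part of the study, finally, 600 patients will be included". The abstract gives the same numbers.
- Section 2.6 (Machine learning): "Data collected from the first 300 patients will be analyzed with neural net". This agrees with 300 in the first stage and gives no size for the second.

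Section 2.7.2 (Statistical analysis) adds a significance level that differs from the 0.01 used for sizing: "For all analysis, *P*-value <.05 will be considered significant".

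**The concern.** A calculated size is a minimum, so it is normally rounded up if it is rounded at all. Here the planned number lies below it, while the text says that the planned number is exactly twice it. A reader who compares the completed study with this article cannot tell whether the target was 600 or 622. Stopping at 600 could be read as under-enrolment against 2.7.1, and the 0.95 power could be quoted for a size that was never planned.

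**Working it through.** **Inputs.** From 2.7.1: calculated size 311, alpha 0.01, power 0.95, odds ratio 3.3, outcome prevalence 30%, doubled for two stages. From the abstract and 2.3: 300 per stage, 600 in total. From 2.7.2: significance level 0.05. Assumption: two-sided tests, since the article does not state sidedness; the one-sided result is also given.

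**1. The plan's own 311.** The article does not print the predictor's distribution, so 311 can be checked for plausibility but not confirmed. Assume logistic regression on one binary predictor (Hsieh formula), with 30% as the overall outcome prevalence P, a share B of patients with the predictor, and p0 and p1 the outcome rates without and with it:

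N = [z(1−α/2)·√(P(1−P)/B) + z(power)·√(p0(1−p0) + p1(1−p1)(1−B)/B)]² / [(p1−p0)²(1−B)]

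At B = 0.20 (p0 = 0.246, p1 = 0.518) this gives N = 331; at B = 0.25 (p0 = 0.233, p1 = 0.501) it gives 290. It returns 311 at B of about 0.22, and again at about 0.66. So 311 is attainable, and it is taken as given below.

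**2. Doubling.**

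- 2 × 311 = 622, against 600 planned: 22 fewer, and 22/622 = 3.5%.
- Per stage, 311 − 300 = 11, and 11/311 = 3.5%.

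**3. Power at 300 and alpha 0.01.** The expected test statistic grows with √n, so no predictor distribution is needed once 311 at 0.95 is accepted:

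power = Φ( [z(1−α/2) + z(0.95)] · √(300/311) − z(1−α/2) )

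- Two-sided: z = 2.576 and 1.645, sum 4.221; √(300/311) = 0.9822; 4.221 × 0.9822 = 4.145; 4.145 − 2.576 = 1.570; Φ = 0.942.
- One-sided: z = 2.326 and 1.645, sum 3.971; × 0.9822 = 3.900; 3.900 − 2.326 = 1.574; Φ = 0.942.

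The loss is about 0.8 percentage points.

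**4. Power at 300 and the 0.05 level of 2.7.2.** The expected statistic at 300 is still 4.145, and only the critical value changes: 4.145 − 1.960 = 2.185; Φ = 0.986.

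**The case against.** The best reply is that 300 is simply 311 in round figures and that nothing follows from it. On size, that stands: under one point of power is lost at the sizing alpha, and power is above 0.95 at the level at which the article says it will test. It does not remove the contradiction, because 2.7.1 claims an exact doubling and no section mentions rounding.

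A reader might infer more than this. Four stronger readings are not supported.

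- **That the trial is underpowered.** Power falls short of 0.95 only at alpha 0.01, and then by less than one point.
- **That 311 is itself wrong because the printed inputs do not determine it.** The share of patients with the predictor and the sidedness are inputs that a condensed article may leave to the full protocol or analysis plan. The result also depends on whether 30% is read as the overall rate or as the rate in patients without the predictor. On the overall reading, 311 is attainable at ordinary predictor shares.
- **That missing data will cut the power much further.** The article gives no rate of incomplete records. An allowance for them is also detail that an article may leave out.
- **That the 0.95 describes how well LUCY performs in stage 2.** Section 2.7.1 sizes the association between input data and the primary outcome, whereas section 2.5 defines the study outcome as LUCY's true positive prediction in stage 2. The figure does not describe that outcome at 311 or at 300.

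**Conclusion.** The contradiction holds: by its own rule, 2.7.1 implies 622 patients, while the abstract and 2.3 plan 600. Each stage is 11 patients, or 3.5%, below its calculated size. The effect on power is small: about 0.942 instead of 0.95 at alpha 0.01, and about 0.986 at the 0.05 level of 2.7.2. These figures assume that 311 patients do give 0.95 power at alpha 0.01 (two-sided for the 0.986) and that the test statistic scales with the square root of the sample size. What needs correcting is the stated size and its power, not the design.

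**What to change.** Restate 2.7.1 along these lines: *We plan 300 patients per stage (600 in total). Given a calculated size of 311 for 95% power, 300 patients give about 94% power at alpha 0.01 for the association between input data and the primary outcome (odds ratio 3.3, outcome prevalence 30%).* Delete the sentence that says enrolment is twice the calculated size.

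The wording should tie the power to that association only, so that it is not read as the power to evaluate LUCY's predictions in stage 2.

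The cost is one or two sentences and a stated power about one point lower. Enrolment, procedures and analysis do not change, and the abstract and sections 2.3 and 2.6 can stand as they are.
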